### Data acquisition

This study has been approved by the local ethics committee of every participated center. The continuous inpatient electronic medical records will be reviewed for sepsis between April 2022 to April 2025. The prevalence of septic myocardial suppression has been reported in previous literature as 10–70% (4), taking the middle value of 40%. With a 95% confidence level, the results were required to fall within 10% of the overall truth rate, and the required sample size was estimated to be at least 1,152 cases. Detailed demographic and clinical characteristics will be collected and recorded, including age, sex, height, weight, primary diagnosis, site of infection, etiology (if known), underlying disease (hypertension, diabetes, coronary artery disease, chronic kidney disease, chronic obstructive pulmonary disease, oncologic disease, autoimmune disease, etc.), and medication history (beta-blockers, digitalis analogs, hormones, immunosuppressive agents, antineoplastic drugs, etc.).

Clinical and laboratory data will be collected included temperature, heart rate, respiratory rate, peripheral oxygen saturation, blood pressure (systolic/diastolic), pH, partial pressure of oxygen, inspired oxygen concentration, Glasgow Coma Scale score, white blood cell count, neutrophil count, lymphocyte count, hematocrit level, platelet count, calcitonin level, G-test scores, serum albumin level, total bilirubin level, serum creatinine level, troponin I level, NT-proBNP level, maximum dose of vasoactive drugs (norepinephrine, dopamine, vasopressin) or cardiac drugs (dobutamine, levosimendan, desacetyl trichothecene), SOFA score, and APACHE II score.

The ultrasound parameters are as follows:

Indicators of left ventricular systolic function: mitral annular plane systolic excursion (MAPSE), LVEF, and left ventricular outflow tract flow velocity time integralIndicators of left ventricular diastolic function: E, A, and *e*'Right ventricular function indicators: tricuspid annular plane systolic excursion (TAPSE), inferior vena cava end-expiratory and end-inspiratory internal diameters, and right/left heart diastolic basal segment transverse diameter ratio (apical four-chamber heart view)Basal status indicators: right ventricular free wall thickness (subxiphoid four-chamber cardiac section) and septal thickness (apical four-chamber cardiac section).

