### Data statistical analysis

SPSS (version 23.0; SPSS Inc., Chicago, IL, USA) will be used for the analysis. Continuous variables will be defined as the mean ± standard deviation, and categorical variables will be presented as percentages. The Kolmogorov–Smirnov test will be used to verify the normality of the distribution of the continuous variables. One-way ANOVA will be used for comparison of means between groups; two independent samples *t*-test will be used for comparison between two groups; χ^2^ test will be used for counting data; and multifactor logistic regression and Cox survival analysis will be used to determine the factors of prognosis. P-values < 0.05 will be considered statistically significant.

The participants will be divided into a modeling cohort and a validation cohort in a 7:3 ratio. In the modeling cohort, variables with *P* < 0.05 in the univariate Cox analysis will be included in the multivariate Cox analysis, and nomogram plots will be constructed. Finally, the validation cohort will be used to evaluate the discrimination ability of the model based on the area under the ROC curve.

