## Discussion

Several studies have confirmed the high mortality rate in patients with sepsis, ranging from 34 to 56% (5) and 33.5% (6) in foreign and domestic countries, respectively, and even higher in patients with combined hyperdynamic left ventricular function or myocardial depression (3, 7). Standardizing the staging of myocardial depression in sepsis and realizing the early identification of patients with sepsis are of great significance for clarifying the cardiac changes in sepsis at various stages, adjusting and guiding treatment in a timely manner, and optimizing hemodynamics.

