In conclusion, this study aimed to obtain data on patients with sepsis from multiple centers across the country, analyze each echocardiographic phenotype of sepsis, and investigate its incidence, duration, and prognosis. The prognosis of various patients can be compared as a predictor of future clinical prognosis, especially in those with “suppressed” and “hyperdynamic” phenotypes. This will be a novel predictor of clinical outcomes in patients with sepsis and the establishment of cardiac ultrasound phenotypes can also serve to guide and educate young physicians.

A limitation of this study may be that patients for whom transthoracic echocardiography data were not available did not undergo further transesophageal ultrasound due to medical constraints at each center and to avoid additional risks and lack of benefit to the patient. It is promising to study subgroups of sepsis patients with other underlying diseases, such as chronic hepatic and renal diseases, autoimmune diseases, and immunosuppressive states, as their underlying diseases may affect the prognosis by influencing the infection status. More specific and sensitive biomarkers for cardiac alterations in sepsis will also be an important area of future research and should be further explored in other studies.

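### The nomogram is drawn from a screened, unpenalised Cox model with about 4 to 7 deaths per listed baseline variable, so its predicted risks are expected to be too spread out, and validation by AUC alone cannot show it

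*Protocol article*

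**What the plan says.** The Data statistical analysis section sets out the prediction model in three steps.

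- **Split.** "The participants will be divided into a modeling cohort and a validation cohort in a 7:3 ratio".
- **Selection and fit.** In the modelling cohort, variables with P < 0.05 "in the univariate Cox analysis will be included in the multivariate Cox analysis, and nomogram plots will be constructed".
- **Validation.** The validation cohort serves to assess discrimination by the area under the ROC curve. No other measure is named.

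The section mentions no penalty, shrinkage, limit on model size or calibration check.

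The only sizing is in Data acquisition, where "the required sample size was estimated to be at least 1,152 cases". It rests on the precision of a prevalence, not on the prediction model. The Discussion gives sepsis mortality "ranging from 34 to 56% (5) and 33.5% (6) in foreign and domestic countries". Data acquisition lists the variables to be collected and says that all of them are recorded at the first time point.

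**The concern.** A nomogram turns a fitted linear predictor into an absolute risk. When many coefficients are estimated without a penalty from few deaths, estimation noise adds variance to that predictor. In new patients the predictions are then spread more widely than the outcomes justify: high predictions are too high and low ones too low. The usual measure is the calibration slope, which is 1 when the spread is right and below 1 when predictions are too extreme.

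Many of the listed items overlap. SOFA and APACHE II stand beside oxygenation, Glasgow Coma Scale, platelets, bilirubin, creatinine and vasoactive doses. White cells stand beside neutrophils, and there are two vena cava diameters. A one-at-a-time screen does nothing to remove such overlap.

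AUC depends only on the ranking of predictions. A nomogram with over-extreme risks could therefore pass the planned validation unnoticed.

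**Working it through.** **The plan's own figure.** For a single proportion, n = z²p(1−p)/d² with z = 1.96 and p = 0.40. With d = 0.10 absolute, n = 92. With d = 0.04 (10% relative), n = 576. The stated 1,152 equals 2 × 576.2, so it needs a doubling that the article does not explain. Nothing below depends on how it was reached; it is used only as the stated minimum.

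**Candidates** (Data acquisition, one parameter per listed item):

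| Group | Count |
|---|---|
| Demographic and diagnostic 7, underlying diseases 7, drug classes 5 | 19 |
| Clinical and laboratory 22, vasoactive or cardiac drugs 6, scores 2 | 30 |
| Ultrasound 3 + 3 + 4 + 2 | 12 |
| Hemodynamic | 4 |
| **Total** | **65** |

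**Deaths.** Modelling cohort: 0.7 × 1,152 = 806.

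- At 33.5% mortality: 806 × 0.335 = 270 deaths, and 270/65 = 4.2 per variable.
- At 56%: 806 × 0.56 = 451 deaths, and 451/65 = 6.9 per variable.

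**Expected shrinkage by formula.** If all 65 parameters enter, the expected uniform shrinkage S solves n = p/[(S−1) ln(1−R²/S)], with p = 65 and n = 806. R² is assumed to be 15, 25, 35 or 45% of its maximum at 33.5% mortality (0.72).

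| R² as share of maximum | S at n = 806 | n needed for S = 0.90 |
|---|---|---|
| 15% | 0.60 | 5,080 |
| 25% | 0.72 | 2,910 |
| 35% | 0.79 | 1,980 |
| 45% | 0.84 | 1,455 |

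**Simulation of the procedure as written.** Settings: 806 patients, 65 candidates of which 10 are true predictors, administrative censoring at day 28, 33.5% mortality, univariate Wald P < 0.05, then a plain Cox fit. The slope is measured in new patients, and the SD of the true log-hazard is 0.7 to 1.0.

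| Assumed structure | Variables entered | Mean calibration slope |
|---|---|---|
| Uncorrelated | about 12 | 0.81–0.91 |
| Pairwise correlation 0.1, same-direction effects | 48–58 | 0.71–0.74 |
| Pairwise correlation 0.2, same-direction effects | 64–65 | 0.59–0.68 |
| Correlation 0.1–0.2, effects of mixed direction | 11–13 | 0.83–0.91 |

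A second set of eight scenarios, with 10 or 20 true predictors and SD 0.6 to 1.2, gave mean slopes of 0.54 to 0.86 at 33.5% mortality, below 1 in 95–100% of runs. At 56% mortality the mean slopes were 0.62 to 0.92, below 1 in 90–100% of runs.

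**What a slope of 0.70 means.** Assume a reference 28-day risk of 30%, so reference survival is 0.7. Take a predicted log-hazard of ±1/0.7 = ±1.43; the average true log-hazard among such patients is ±1.

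- Predicted 1 − 0.7^exp(1.43) = 77%; average actual 1 − 0.7^exp(1) = 62%.
- Predicted 1 − 0.7^exp(−1.43) = 8%; average actual 1 − 0.7^exp(−1) = 12%.

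**The case against.** **The candidate list is not in the article.** The 65 items are data to be collected, and nothing says that every one enters the screen. A fuller plan could name fewer candidates or add shrinkage. This stands as a limit on the size of the problem. Multi-category items and the open-ended entries would raise the count, while clinical pre-selection would lower it. It does not remove the point, because the selection rule, the multivariate fit and the single validation measure are written down.

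**The low slopes need particular conditions.** This also stands. Slopes of 0.6 to 0.75 arise when candidates are positively correlated and their effects run in the same direction. With mixed directions at the same correlations, the slope returns to about 0.8 to 0.9. The article gives no correlations.

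**The inputs are cautious.** The 1,152 is a minimum and 33.5% is the lowest mortality quoted. At 56% the expected slope is still below 1, though sometimes only slightly.

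A reader might also infer more than the documents support:

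- *That a patient whose true risk is 62% would be told 77%.* This reverses the calibration slope, which describes patients grouped by prediction. Predicted log-hazard regressed on true log-hazard had a slope of about 0.90 to 1.07 in simulation, so there is no such systematic shift by true risk.
- *That each echo coefficient is inflated.* Selected true predictors averaged 0.91 to 1.08 of their true coefficient. The slope falls mainly because noise widens the score.
- *That the later recordings enter the model too.* The article does not say so.
- *That the nomogram is the study's bedside product.* It is mentioned once. The stated aims are phenotype prevalence and association with prognosis. The closing remark that "The prognosis of various patients can be compared as a predictor of future clinical prognosis" concerns comparing patients by phenotype, not a nomogram.

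**Conclusion.** The concern holds as an expectation, not a certainty. Followed as written, the rule is expected to give a nomogram whose risks are too spread out: mildly (slope about 0.8 to 0.9) if candidates are uncorrelated or their effects differ in direction, and markedly (about 0.6 to 0.75) if they are positively correlated with same-direction effects. This rests on the minimum sample size, the quoted mortality range, the listed variables as candidates, and assumed predictor strength and correlation. The planned AUC cannot distinguish these cases. The point concerns absolute predicted risks. It does not touch the mortality outcomes, the phenotype comparisons or the direction of any echo effect.

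**What to change.** In Data statistical analysis, replace the screened plain fit by one of these:

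1. a penalised Cox model (ridge or elastic net, penalty chosen by cross-validation) on baseline candidates named in advance; or
2. the Cox model with its coefficients multiplied by a bootstrap shrinkage factor, the univariate screen being repeated in every resample and the baseline hazard then re-estimated.

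Draw the nomogram from the shrunken coefficients. Report the calibration slope and a calibration plot beside the AUC; the validation cohort already planned would have about 346 × 0.335 = 116 deaths for this.

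In three simulated scenarios at 33.5% mortality with 806 patients, cross-validated ridge moved the mean slope from 0.80, 0.70 and 0.65 to 0.97, 1.06 and 1.07. Modelling all 1,152 patients without shrinkage reached only 0.88, 0.77 and 0.76, so dropping the split would not be enough.

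The cost is wording and some programming, possibly outside the named package, and smaller nomogram weights. Uniform shrinkage leaves the AUC unchanged. No new data or patients are needed.

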The hemodynamic parameters will be collected included the central venous pressure, central venous–arterial blood carbon dioxide partial pressure difference, central venous oxygen saturation, and arterial blood lactate concentration.

All parameters mentioned above will be recorded within 2 h after sepsis diagnosis in the ICU, followed by recording of the ultrasound parameters and hemodynamic parameters once at 24, 72 h, and 7 days.

The prevalence of each phenotype will be described firstly. The primary outcomes are in-hospital and 28-day mortality rates. The secondary outcomes are the degree of echocardiographic improvement on day 7, length of stay in the ICU, and number of days on mechanical ventilation. Severe and irreversible disease will be determined by the supervising physician, and the patient's family chose automatic discharge due to local customary conditions indicating death.

If a respondent is absent at a point in time when access is required, resulting in missing data at that point in time, or if an ending visit is missed, data from other points in time can be included in the analysis for that point in time without affecting the integrity and accuracy of the data at other points in time. We will ensure that the data collection was standardized and controllable, with the advantages of complete information, consistent structure, and no redundant information. In the process of data collection, we use the case report form to extract the clinical information required for the study from the research subjects, convert it into a standardized data form, and construct a reasonable database.

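### The only stated validation is the ROC area of the whole nomogram, with no comparison to the same model without the cardiac phenotype, so a good value cannot support the claim that the phenotype is a novel predictor

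*Protocol article*

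**What the plan says.** All of the prediction plan is in the second paragraph of Data statistical analysis:

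- Split: "The participants will be divided into a modeling cohort and a validation cohort in a 7:3 ratio".
- Selection: variables with P below 0.05 "in the univariate Cox analysis will be included in the multivariate Cox analysis, and nomogram plots will be constructed".
- Validation: "Finally, the validation cohort will be used to evaluate the discrimination ability of the model based on the area under the ROC curve".

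No list of model terms, reference model, difference in ROC area or success threshold is given. Nothing requires the phenotype to be in the nomogram.

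The candidates are the variables listed under Data acquisition. They include "SOFA score, and APACHE II score" and, among the hemodynamic parameters, "central venous oxygen saturation, and arterial blood lactate concentration". These are listed as collected; the article does not say that they are terms of the model.

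The aim in the Abstract is the relation between ultrasound phenotype and prognosis. The closing part of the Discussion says of the phenotype comparison: "This will be a novel predictor of clinical outcomes in patients with sepsis". Separately, the first paragraph of Data statistical analysis plans multivariable logistic and Cox regression to find prognostic factors.

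**The concern.** The ROC area of a combined model measures how well all its terms together rank patients by risk. It does not identify what any one term contributes. If severity variables pass the screen and predict death, the area will be respectable whether the phenotype matters or not, and even if the screen has removed it.

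The study's interest is in the phenotype, yet the one validation step is silent on it. A nomogram reported with a validated ROC area could be taken as evidence for ultrasound phenotyping when the severity scores alone would have given the same figure.

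**Working it through.** **Inputs from the protocol article.** Total 1,152 ("the required sample size was estimated to be at least 1,152 cases"); 7:3 split; screen and significance level 0.05, taken as two-sided; mortality 33.5% (the domestic figure in the Discussion).

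**The plan's own figure.** The 1,152 comes from a prevalence calculation (40%, 95% confidence, within 10%). Relative precision gives 1.96² × 0.6 / (0.4 × 0.1²) = 576.2; absolute precision gives 1.96² × 0.4 × 0.6 / 0.1² = 92.2. The stated number appears only as 2 × 576.2 = 1,152.4, a doubling the text does not mention. That is a separate matter; 1,152 is used here as stated. The article gives no figure for the ROC area.

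**Step 1: size of the validation cohort.** 0.3 × 1,152 ≈ 346 patients, leaving 806 for modelling. Deaths: 0.335 × 346 ≈ 116, with 230 survivors.

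**Step 2: what the whole-model area shows by itself.** Hanley-McNeil variance for area A: [A(1−A) + (n₁−1)(Q₁−A²) + (n₀−1)(Q₂−A²)] / (n₁n₀), where Q₁ = A/(2−A), Q₂ = 2A²/(1+A), n₁ = 116 and n₀ = 230. For A = 0.65: (0.2275 + 6.783 + 20.523) / 26,680 = 0.001032, so SE = 0.0321. The null SE is √(347 / (12 × 26,680)) = 0.0329, so an area above 0.5 + 1.96 × 0.0329 = 0.5645 is significant.

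| True area | SE | P(significantly above 0.5) | P(observed ≥ 0.70) |
|---|---|---|---|
| 0.55 | 0.0331 | 33% | about 0% |
| 0.60 | 0.0328 | 86% | 0.1% |
| 0.65 | 0.0321 | 99.6% | 6% |
| 0.70 | 0.0310 | about 100% | 50% |
| 0.75 | 0.0293 | about 100% | 96% |
| 0.80 | 0.0270 | about 100% | about 100% |

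Both bars are assumptions, since the article sets none.

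**Step 3: the stated pipeline, simulated.** There were 300 runs per row: 7:3 split, univariate Cox screen, multivariable Cox, 28-day ROC area in the 346. The assumptions, none of them from the article, are three severity variables correlated 0.5 with each other, suppressed phenotype 40%, hyperdynamic 20%, exponential survival, and a latent phenotype-severity correlation of 0.3. The last column is the 2-df likelihood-ratio test of the phenotype terms in all 1,152.

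| Log HR per severity variable | Suppressed-phenotype HR | Whole-model area | Area without phenotype | Mean difference | Beats 0.5 | ≥ 0.70 | Phenotype passes screen | Joint test rejects |
|---|---|---|---|---|---|---|---|---|
| 0.12 | 1.0 | 0.594 | 0.596 | −0.0018 | 82% | 0% | 23% | 7% |
| 0.2 | 1.0 | 0.658 | 0.659 | −0.0011 | 100% | 11% | 44% | 5% |
| 0.3 | 1.0 | 0.726 | 0.727 | −0.0008 | 100% | 80% | 69% | 6% |
| 0.4 | 1.0 | 0.781 | 0.781 | −0.0006 | 100% | 99.7% | 85% | 5% |
| 0.2 | 1.3 | 0.670 | 0.666 | 0.0031 | 100% | 18% | 92% | 55% |
| 0.3 | 1.3 | 0.735 | 0.733 | 0.0019 | 100% | 87% | 98% | 57% |
| 0.2 | 1.5 | 0.680 | 0.670 | 0.0099 | 100% | 26% | 99.7% | 91% |
| 0.3 | 1.5 | 0.742 | 0.736 | 0.0062 | 100% | 92% | 100% | 94% |

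(298 runs counted in the first row; in the other two no severity variable passed the screen.)

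**Step 4: reading the table.**

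- Moving from no effect to HR 1.5 shifts the whole-model area by 0.680 − 0.658 = 0.022 or 0.742 − 0.726 = 0.016. Both are below one standard error (about 0.03). Without the reference area, a reader cannot tell the two situations apart.
- With phenotype and severity uncorrelated and no phenotype effect, a phenotype term entered the model in only 10-11% of runs. The area still beat 0.5 in 83-100%. The validation can look good for a model that does not contain the phenotype.
- With correlation 0.3, a null phenotype passes the screen in 23-85% of runs but is significant after adjustment in the modelling cohort in only about 3-5%. It can therefore sit in a nomogram with a good area while contributing nothing.

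**The case against.** The strongest reply has four parts.

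**The article validates the model, not the phenotype.** This is correct. ROC area is a standard measure of a nomogram's discrimination, and no sentence says that it proves the phenotype's value. The point is only that the one validation offered does not bear on the phenotype aim or on the Discussion's claim.

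**An adjusted phenotype effect is already planned.** This largely stands. The multivariable logistic and Cox analysis of prognostic factors is not confined to the modelling cohort. In a two-variable logistic simulation on all 1,152, the Wald test of the phenotype coefficient and the nested likelihood-ratio test agreed in every replicate (4-6% rejection under no effect, 85-87% at odds ratio 1.5). What is missing is a fixed covariate set, a guarantee that the phenotype is retained, and any validation of what it adds.

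**The article is condensed, so a reference model may be in the full plan.** The article does commit itself to a split, a selection rule and a validation measure. The criticism is that this stated choice does not fit the stated claim, not that detail is absent.

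**The proposed difference in area is itself insensitive.** This is true: 0.002-0.010 on average with a real effect. That is why the inference should rest on the adjusted hazard ratio and joint test, with the areas as description.

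A reader might go further and infer that the validation will almost always succeed, in a model known to contain SOFA, APACHE II and lactate. The documents do not support that. Those variables are only candidates, and no success criterion is stated. Under an assumed bar of 0.70 the result runs from 0% to 99.7% of runs, depending on how strong the severity variables are taken to be.

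**Conclusion.** The concern holds in limited form. The whole-nomogram ROC area cannot show whether the cardiac phenotype adds prognostic information, because the model is filled by a screen that may admit severity variables and drop the phenotype, and no model without the phenotype is fitted. That conclusion follows from the stated method and needs no particular effect size.

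The size is conditional. With no phenotype effect, the area beats 0.5 in 82-83% of runs at a model area near 0.60 and in all runs at 0.66 or above, while including or omitting the phenotype changes it by 0.002 or less on average. These figures rest on the assumed severity strength, phenotype frequencies, correlation and survival model.

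The data and the planned adjusted analysis are unaffected. This is a cheap improvement that should be made, not a flaw that invalidates the study.

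**What to change.** In Data statistical analysis:

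1. Pre-specify a clinical reference model from baseline variables already collected (for example age, SOFA or APACHE II, and lactate).
2. Add the first-scan phenotype as forced terms, whatever the univariate screen shows.
3. Base the prognostic claim on the adjusted hazard ratios with confidence intervals and the joint likelihood-ratio test of the phenotype terms in the full cohort.
4. In the validation cohort, report the ROC area of both models and their difference with a confidence interval.
5. Describe the whole-nomogram ROC area as performance of the combined model only.

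The cost is one extra model fit on data already collected and a few lines of text. The drawback is that the gain in area will probably look small and imprecise. At HR 1.5 it averaged 0.0062 and 0.0099, with standard deviations across runs of 0.0091 and 0.0132, so an interval for the difference will often include zero even when the joint test is positive (91-94% of runs).
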